## Abstract

**Background:**

Generalized anxiety disorder (GAD) is a chronic mental health condition that results in a significant individual and societal burden. While cognitive behavioral therapy (CBT) is well established as an efficacious treatment for GAD, many patients experience logistical barriers when accessing face-to-face CBT. Remotely delivered treatments remove many of these barriers. Despite emerging evidence demonstrating the efficacy of remotely delivered CBT for GAD, studies examining the efficacy of remote methods for GAD that are analogous to standard face-to-face treatment, in particular synchronous treatments such as CBT delivered via online videoconferencing (VCBT), are needed.

**Methods:**

The authors propose a two-group randomized controlled trial comparing the efficacy of VCBT for GAD against a waitlist control group. The recruitment target will be 78 adults with primary GAD of at least moderate severity. The manualized high-intensity VCBT intervention will be delivered weekly over a 10-week period. After treatment completion, waitlist participants will receive the same VCBT delivered in a brief format (i.e., weekly over a 5-week period). Treatment for both groups will be delivered in real time via an online teleconferencing platform. Outcome measures will be administered at baseline, mid-treatment, post-treatment, and 3-month follow-up.

**Discussion:**

This trial will report findings on the efficacy of a remote synchronous high-intensity VCBT intervention for GAD. The results have the potential to contribute towards advancing our knowledge on the evidence base for GAD, as well as increase the dissemination of VCBT for GAD.

**Trial registration:**

Australian New Zealand Clinical Trials Registry ACTRN12621000786897. Registered on 22 June 2021

## Introduction

Generalized anxiety disorder (GAD) is characterized by excessive and uncontrollable worry that is accompanied by a number of physical and/or cognitive symptoms [1]. The disorder is often chronic [22] and results in considerable individual and economic burden [27, 48]. GAD can be effectively treated with cognitive behavioral therapy (CBT) [11]; however, numerous barriers to accessing treatment exist including cost, difficulty accessing a trained clinician, and geographical isolation [10, 16, 37, 40]. One way to overcome these barriers is to provide specialized treatment remotely, using digital health technologies.

Remotely delivered treatments do not require the clinician and the client to be in the same location and these interventions can be provided in either a low-intensity or high-intensity fashion [54]. Low-intensity remote treatments involve the client working through largely self-help materials either online or via a workbook, accompanied by brief asynchronous clinician contact (i.e., 10 min per week by telephone or email). High-intensity remote treatments involve using digital health technologies to provide synchronous sessions that are analogous to standard face-to-face treatment. While low-intensity remote treatments have been demonstrated to be efficacious in the treatment of GAD, with several studies demonstrating medium to large pooled effects across studies [2, 43], there is limited evidence examining high-intensity remote treatments for this condition [50]. The literature that does exist has considerable limitations (i.e., uncontrolled studies with small samples sizes) [42]. Thus, the efficacy and acceptability of high-intensity remote CBT for GAD requires further investigation.

One promising remote high-intensity approach to treatment includes Internet videoconferencing-delivered CBT (VCBT). VCBT involves the therapist and client working together over video-link, maintaining the visibility of the therapist, and clients’ non-verbal behaviors. Recent research has demonstrated that high-intensity remote CBT results in equivalent outcomes compared to traditional face-to-face treatment across a number of common mental health disorders [51]. While there has been little research investigating the efficacy of VCBT for GAD specifically, case study results have been promising. For example, Bouchard and Renaud [5] demonstrated that VCBT resulted in significant improvements from pre-treatment to post-treatment in GAD symptoms. Similar results were found in a case study by Théberge-Lapointe et al. [47], and this study further demonstrated that the effects of VCBT were durable, with results maintained up to 12 months post-treatment [47]. Importantly, the therapeutic alliance does not appear to be affected when CBT is delivered in this format [5, 52].

This study describes the procedures and methodology of a randomized controlled trial (RCT) investigating the efficacy and acceptability of VCBT for GAD. Based on the limited existing literature, it is hypothesized that high-intensity VCBT will (1) be acceptable to individuals with GAD; (2) result in significant reductions in symptoms, resulting in large within-group at pre-treatment and follow-up and large between-group effect sizes at 3-month follow-up; and (3) brief VCBT will result in outcomes similar to those seen in standard length face-to-face treatment. It is anticipated that the results of the proposed study will inform best-practice psychological treatment for GAD.

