## Materials and method

### Participants

Seventy-eight individuals will be recruited for this study. To be included in the trial, participants are required to (1) be an Australian resident, (2) be aged 18 or above, (3) meet criteria for GAD as the primary disorder, (4) experience symptoms of at least “moderate severity,” and (5) be on a stable dose of psychotropic medication. Participants will be excluded if they have symptoms that will put them at risk of harming themselves or others or will confound results of the treatment. Participants will also be excluded if they do not have regular access to the Internet and camera. A complete list of inclusion and exclusion criteria is outlined in Table 1.

**Table 1 Tab1:** Study inclusion and exclusion criteria with rationale

Inclusion criteria	Rationale
1. Australian resident	Study population
2. Aged 18 or above	Study population
3. Fluent in English	Treatment confound/participant concern
4. Meet criteria for GAD as primary disorder and disorder is of at least “moderate severity” (defined as a score of 4 on the DIAMOND module severity measure)	Study population
5. Medication free or on a stable dose of psychotropic medication	Treatment confound
6. Not currently receiving regular psychological services for their GAD symptoms (defined as sessions at least once a week with a qualified mental health professional)	Treatment confound
Exclusion criteria	Rationale
1. Severe depressive symptoms as assessed by a score of 20 or above on the PHQ-9	Participant safety
2. Are at suicide risk as assessed by a score of “2” (more than half the days) or higher on item 9 of the PHQ-9 on the screening questions or via clinician judgment during the telephone interview using the C-SSRS	Participant safety
3. Engage in daily alcohol use or daily illicit drug use	Treatment confound
4. Presence of a schizophrenia spectrum disorder as assessed by the DIAMOND	Treatment confound
5. Significant cognitive/intellectual impairment as assessed during diagnostic interview	Treatment confound
6. Medical condition that may interfere with treatment	Treatment confound
7. Do not have access to a computer with a camera and stable internet on a regular basis	Feasibility

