### Design

A CONSORT-R compliant 2-group RCT superiority trial will be used to investigate the research questions. Participants will be randomly assigned to an immediate treatment group (*n* = 39) or a waitlist control group (*n* = 39). Group 1 will receive immediate access to a manualized high-intensity VCBT intervention. Group 2 will receive treatment after group 1 completes treatment. Given this is the first controlled trial investigating VCBT for GAD, a waitlist control group was considered appropriate. The content and design of this RCT are in accordance with the guidelines for clinical trial protocols as specified by the Standard Protocol Items: Recommendations for Interventional Trials (SPIRIT) 2013 statement [9]. The SPIRIT checklist was followed to ensure compliance.

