### Data storage and analysis

In order to maintain confidentiality, all electronic data (including session recordings and other identifiable information) will be stored on a password-protected computer that is only accessible to members of the research team. All hardcopy data will be stored in a locked filing cabinet in the chief investigators locked office.

Group differences in demographic data and pre-treatment measures will be analyzed with independent samples *t*-tests with Bonferroni-corrected *p-*values (continuous measures) and *chi*-square tests (categorical measures). Treatment acceptability will be examined using descriptive statistics. The main analyses comparing the treatment group to the control group will be carried out using conservative intention-to-treat principles and using mixed-linear models with an unstructured covariance structure. Multiple imputation will be used to handle missing data. Effect sizes using Cohen’s *d* will be calculated for within-group and between-group differences, based on pooled standard deviations for both the entire sample using the estimated marginal means and completer sample (i.e., those who completed post-treatment and 3-month follow-up questionnaires). All analyses will be conducted based on the total score of the relevant outcome measure. The efficacy and acceptability of the brief treatment will be examined in the same manner described above. Comparisons between standard treatment and brief treatment will be analyzed using benchmarking analyses using the procedure outlined by Minami et al. [36]. All analyses will be performed using IBM SPSS Statistics (version 26). Results will be disseminated via national and international conference presentations, as well as in peer-reviewed journal articles. Participants are able to access publications resulting from the study by contacting the chief investigator.

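### Hypothesis 2 places a within-group effect at baseline, never names post-treatment, and puts its only between-group contrast at a time when the waitlist should already have been treated

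*Protocol article*

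**What the plan says.** The Introduction states three hypotheses. The second is the efficacy hypothesis. It predicts that VCBT will "result in significant reductions in symptoms, resulting in large within-group at pre-treatment and follow-up" "and large between-group effect sizes at 3-month follow-up". The two parts are joined, so both are predicted.

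Elsewhere the article describes a controlled comparison. Design: "A CONSORT-R compliant 2-group RCT superiority trial will be used to investigate the research questions". Data storage and analysis: "The main analyses comparing the treatment group to the control group will be carried out using conservative intention-to-treat principles", with mixed linear models. The same section adds: "Effect sizes using Cohen’s *d* will be calculated for within-group and between-group differences, based on pooled standard deviations".

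On the control arm, Design says: "Group 2 will receive treatment after group 1 completes treatment". The Treatment section gives that later treatment as five weekly sessions. Table 2 schedules the GAD-7, the primary outcome, at pre-treatment, mid-treatment, post-treatment and 3-month follow-up.

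**The concern.** Hypothesis 2 has two faults as printed.

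- **An impossible time point.** A within-group effect is a change from baseline. At baseline it is zero by definition, so that part cannot be tested. The occasion that was probably meant, post-treatment, appears nowhere in the hypothesis.
- **A between-group prediction at the wrong time.** By 3-month follow-up the waitlist should have had its own course of VCBT, so the comparison is between standard and brief treatment. The occasion on which randomisation gives a clean comparison with no treatment is left out.

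Together these leave the efficacy hypothesis without a contrast that answers the efficacy question. What remains is change over time within the VCBT arm, which includes natural course and any regression to the mean. The waitlist exists to remove those. At stake is which result is read as the answer to the trial's main question.

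**Working it through.** **1. The plan's own figures.** The Power section gives d = 0.80, alpha 0.05, power 0.80 and 34 per group, and names no time point. A two-sided t-test for d = 0.80 needs 26 per group for 80% power, and 34 per group gives 90%. The stated size therefore errs on the safe side and does not bear on this point. With 34 per group the difference detectable with 80% power is d = 0.69.

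**2. Time points side by side.**

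| Occasion (Table 2) | Within-group prediction in hypothesis 2 | Between-group prediction in hypothesis 2 | State of waitlist |
|---|---|---|---|
| Pre-treatment | Yes (change is zero by definition) | No | Untreated |
| Post-treatment | No | No | Untreated |
| 3-month follow-up | Yes | Yes | Brief VCBT due and, if prompt, finished |

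**3. State of the waitlist at follow-up.** Inputs: 10 weeks of standard treatment, 5 weeks of brief treatment, and a follow-up 3 months (about 13 weeks) after the immediate group's post-treatment.

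- Immediate group's follow-up: week 10 + 13 = 23.
- Brief treatment, if started at once: weeks 10 to 15, so it ends 23 − 15 = 8 weeks before follow-up.
- With a delay of w weeks, it is finished by follow-up if w ≤ 8 and has begun if w < 13.

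**4. Effect on the contrast that is named.** Let δ be the effect of standard VCBT against no treatment, still present at follow-up, and f the fraction of it that brief VCBT delivers. The follow-up contrast is then δ(1 − f). With δ = 0.80, it falls below the detectable 0.69 once f exceeds 1 − 0.69/0.80 = 0.14. At f = 0.5 it is 0.40. The article gives no value for f, but hypothesis 3 expects brief VCBT to perform much like full-length face-to-face treatment. That sits badly with a large difference between the arms at follow-up.

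**5. What within-group change can show alone.** This is an illustration with assumed values: 34 per arm, no treatment effect, both arms improving by s SD, pre-post correlation r from 0.3 to 0.7. The standardised paired change is s / √(2(1 − r)). For s = 0.5 and r = 0.5 it is 0.5 / √1 = 0.5, and the paired t-test has power 0.81. Observed d was simulated (20,000 trials per setting).

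| Shared change s | Significant reduction in VCBT arm | Observed within-group d ≥ 0.80 |
|---|---|---|
| 0.3 | 0.30 to 0.59 | 0.00 to 0.01 |
| 0.5 | 0.67 to 0.96 | 0.03 to 0.08 |
| 0.8 | 0.97 to 1.00 | 0.50 to 0.51 |

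In the same settings a test against an untreated waitlist rejects in 5% of trials, and an observed between-group d of 0.80 or more occurs in about 0.1%. A significant reduction within the arm is thus easy to obtain without any treatment effect. A large one is rare unless the shared change is itself near 0.8 SD.

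**The case against.** The main objection is that the article never makes within-group change the test of efficacy, and this stands. Hypothesis 2 joins its two parts, so a large within-group effect with a small between-group difference would fail it as written. The main analysis compares treatment with control, the trial is declared a superiority trial, and Cohen's d accompanies that analysis. A reader might infer that the plan lets within-group change alone confirm efficacy, but the documents do not support that.

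A reader might also infer that the treatment effect would be overstated by 33% to 100%. The arithmetic exists: an assumed waitlist gain of 0.2 with a true effect of 0.6, or 0.4 with 0.4, each sums to 0.80, and 0.80/0.6 = 1.33 while 0.80/0.4 = 2.0. But the waitlist gains are assumed, and the figure applies only if within-group d is reported as the treatment effect, which the article does not propose.

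Regression to the mean is also less direct than it looks. Entry requires participants to "Meet criteria for GAD as primary disorder and disorder is of at least" moderate severity on the DIAMOND module, whereas the outcome is the GAD-7, which Table 2 lists at pre-treatment and not at screening. Selection on one instrument causes less regression on another measured later. Natural course and treatment-seeking remain as sources of shared change, of unknown size.

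Finally, the wording may be a slip for post-treatment, or may mean change from pre-treatment to follow-up. Either is plausible. The second reading still leaves post-treatment unnamed, and neither reading repairs the between-group part.

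**Conclusion.** Hypothesis 2 is wrong as written and should be corrected. The baseline time point is certain from the text and Table 2, as is the absence of post-treatment. That the between-group contrast comes after the waitlist's treatment follows from the Design and Treatment sections. It assumes that brief treatment starts within about 8 weeks of the immediate group finishing; with a start delayed by 13 weeks or more, the waitlist would still be untreated at follow-up. The article states no such delay.

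The consequence is limited to the hypothesis. It names no contrast with an untreated control, and its only part bearing on VCBT against no treatment is uncontrolled. The planned main analysis can still supply the right comparison. The document supports no numerical bias in the treatment effect, and the probabilities above illustrate the principle under assumed shared change and correlation.

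**What to change.** 1. In hypothesis 2, replace pre-treatment with post-treatment and supply the missing noun after within-group.
2. State that efficacy is judged by the randomised VCBT-versus-waitlist difference in GAD-7 at post-treatment, taken while the waitlist is still untreated. This agrees with the main analysis in Data storage and analysis.
3. Label within-group Cohen's d as descriptive, and likewise any between-group figure at 3-month follow-up, with a note that the waitlist will by then have been offered brief VCBT.

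The cost is wording only. Table 2 already schedules the GAD-7 at every occasion needed, assuming that its post-treatment column, which is not split by arm, applies to the waitlist when the immediate group finishes. No visit, participant or change to treatment timing is required.

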### Treatment

Treatment will be provided at a university outpatient clinic in Australia and will follow a manualized VCBT intervention which is informed by the Intolerance of Uncertainty Model of GAD [13, 44]. Such CBT interventions have been found to be efficacious in previous clinical trials for GAD [29]. Those in the immediate treatment condition will receive 10 weekly (50 min) treatment sessions to be conducted via Zoom [57]. The treatment for this group will comprise six modules and will cover the following: (1) psychoeducation, (2) cognitive restructuring to challenge positive beliefs about worry, (3) behavioral experiments to develop a greater tolerance to uncertainty, (4) problem solving training to reduce negative problem orientation, (5) imaginal exposure to address cognitive avoidance, and (6) relapse prevention. The treatment protocol is outlined in Table 3. Participants will also be required to complete homework tasks between sessions. When the immediate treatment group concludes treatment, the control group will receive a brief manualized version of the same treatment taking place over 5 weeks (i.e., 5 weekly, 50-min sessions). The same interventions will be covered; however, a smaller number of sessions will be dedicated to each intervention (see Table 3). After the post-treatment assessment, participants are encouraged to consult with the primary care physician if they require ongoing treatment for their symptoms of GAD or other mental health conditions.

**Table 3 Tab3:** Treatment protocol

Standard treatment		Brief treatment	
Session	Module	Session	Module
1	Psychoeducation	1	Psychoeducation
2	Cognitive restructuring	2	Cognitive restructuring and problem solving training
3	Cognitive restructuring	3	Behavioral experiments
4	Problem solving training	4	Imaginal exposure
5	Cognitive restructuring and problem solving training	5	Relapse prevention
6	Behavioral experiments		--
7	Behavioral experiments		--
8	Imaginal exposure		--
9	Imaginal exposure		--
10	Relapse prevention		--

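### Hypothesis 2 places the between-group effect at 3-month follow-up, when the waitlist arm has already received brief VCBT, so that contrast cannot estimate VCBT versus waitlist

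*Protocol article*

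**What the plan says.** **Hypothesis 2 (Introduction).** The predicted reductions are described as "resulting in large within-group at pre-treatment and follow-up and large between-group effect sizes at 3-month follow-up". The between-group prediction has one time point, 3-month follow-up. The within-group prediction is partly placed at pre-treatment, where no treatment effect can exist.

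**Timing of control treatment.** Design: "Group 2 will receive treatment after group 1 completes treatment". Treatment: "When the immediate treatment group concludes treatment, the control group will receive a brief manualized version of the same treatment", given as five weekly sessions. The Abstract agrees. No section keeps the waitlist arm untreated until follow-up.

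**Assessments (Table 2).** The GAD-7 and all secondary outcomes are collected at pre-treatment, mid-treatment, post-treatment and 3-month follow-up. The waitlist arm has no separate column or exception.

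**Analysis (Data storage and analysis).** "The main analyses comparing the treatment group to the control group will be carried out using conservative intention-to-treat principles", with linear mixed models and an unstructured covariance. No time point is named for the between-group contrast. Effect sizes are also planned for a completer sample, defined as "those who completed post-treatment and 3-month follow-up questionnaires".

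**Hypothesis 3 (Introduction).** "brief VCBT will result in outcomes similar to those seen in standard length face-to-face treatment".

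**The concern.** The trial is described as a superiority trial against a waitlist. A waitlist answers the efficacy question only while it is still waiting. At 3-month follow-up, randomisation still supports a comparison, but of a different kind: ten sessions given at once against five sessions given later.

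A difference at that time would not show that VCBT beats no treatment. The absence of one could mean that both formats work. Because the analysis section does not name a time, nothing in the article moves the efficacy claim back to the interpretable contrast, and the choice between post-treatment and follow-up could be made after results are seen.

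**Working it through.** **1. Timeline.** The inputs are ten weekly sessions in the immediate arm and five in the waitlist arm (Treatment). Three months is taken as 12 to 13 weeks. The weeks are inferred from the session schedule, because the article gives no assessment clock from randomisation.

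- Immediate arm treated: weeks 0 to 10.
- Waitlist arm treated: about week 10 to 10 + 5 = 15.
- Follow-up counted from the end of immediate treatment: 10 + 12 = 22 to 10 + 13 = 23, which is 7 to 8 weeks after the waitlist arm finishes VCBT.
- Follow-up counted from the waitlist arm's own treatment: 15 + 12 = 27 to 15 + 13 = 28, also after VCBT.

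On either clock there is no untreated control at the hypothesised time. Post-treatment in the immediate arm, at about week 10, is the last scheduled assessment at which an untreated control can exist.

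**2. The plan's own power figure.** The Power section gives alpha 0.05, power 0.80, d = 0.80 and 34 per group. Sidedness is not stated. With a two-sided two-sample t-test, 80% power needs 25.5, so 26 per group. With 34 per group the power is 0.902, and 90% power needs 33.8. The stated 34 therefore fits 90% power, not 80%. This gap is on the conservative side and the present point does not depend on it.

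**3. What remains at follow-up.** Assume that standard VCBT has d = 0.80 against no treatment, that this is maintained to follow-up, and that brief VCBT achieves a fraction f of it. The documents give no value for f, so a range is shown.

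- Remaining difference: d = 0.80 × (1 − f).
- Noncentrality: d × √(n/2). With n = 34, √17 = 4.123 and there are 66 degrees of freedom.
- Power: two-sided noncentral t at 0.05.

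| f | d at follow-up | Noncentrality | Power, 34 per arm | Power, 39 per arm |
|---|---|---|---|---|
| 0 (no control treatment, as at post-treatment) | 0.80 | 3.298 | 0.902 | 0.937 |
| 0.25 | 0.60 | 2.474 | 0.684 | 0.744 |
| 0.50 | 0.40 | 1.649 | 0.369 | 0.415 |
| 0.75 | 0.20 | 0.825 | 0.128 | 0.141 |
| 1 | 0 | 0 | 0.05 | 0.05 |

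**4. The reverse question.** For d = 0.80 to remain at follow-up, the standard effect would have to be 0.80 / (1 − f). That is 0.80 / 0.5 = 1.6 if brief VCBT achieves half of it, and 0.80 / 0.25 = 3.2 if it achieves three quarters.

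**5. Hypotheses 2 and 3 side by side.** Hypothesis 3 compares brief VCBT with standard-length face-to-face treatment. The Introduction also states that "high-intensity remote CBT results in equivalent outcomes compared to traditional face-to-face treatment", across common mental health disorders. If both hold for GAD, brief and standard VCBT should end up close together, f is near 1, and the expected follow-up difference is near zero rather than large.

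**The case against.** The strongest reply is that this is a drafting slip. The same sentence puts a within-group effect at pre-treatment, so the wording is visibly garbled. The Abstract states the aim as efficacy against a waitlist, and Table 2 collects the GAD-7 at mid- and post-treatment. All of this stands, and it means that the error lies in the stated time point and not in the whole design. It does not remove the error, because no other section names the contrast time. Nor can it be left to an analysis plan that is not shown: the article states a time that conflicts with its own treatment schedule.

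A reader might infer more than the documents support:

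- *Hypotheses 2 and 3 cannot both be true.* Hypothesis 3 has an external face-to-face comparator, and standard-versus-brief comparisons are assigned to benchmarking. The tension arises only by implication, through the equivalence premise.
- *An effective treatment would give a null result at follow-up.* It could. That result is expected only if brief VCBT fully matches standard VCBT; at half the effect, d = 0.40 remains.
- *The main test is diluted by including follow-up.* No pooled or omnibus test is specified. With unstructured covariance, a post-treatment contrast can be estimated for that visit, so follow-up need not be dropped from the model.
- *The completer definition undermines the main analysis.* It affects supplementary effect sizes only, beside whole-sample estimates under intention to treat. It remains a minor flaw: a control participant's inclusion, even for the post-treatment effect size, depends on responding after brief VCBT.
- *No between-group comparison at follow-up is legitimate.* Immediate standard versus delayed brief is a valid randomised comparison if it is labelled as such.

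**Conclusion.** Hypothesis 2 is wrong as written and should be corrected before results are seen. On the article's own schedule, "large between-group effect sizes at 3-month follow-up" cannot be evidence for VCBT over waitlist, because the control arm has been treated by then. This conclusion needs no power assumption; it rests on the treatment sequence, with week numbers inferred from the session counts.

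The size of the problem does rest on assumptions: a maintained standard effect of 0.80, 34 analysed per arm, a two-sided 0.05 test, and an unknown fraction achieved by brief VCBT. Within the range of one half to three quarters, power at follow-up is about 37% to 13%, against about 90% at post-treatment. The tension with hypothesis 3 is secondary, and the main conclusion does not depend on it.

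**What to change.** - Reword hypothesis 2 and the analysis section so that the single primary between-group contrast is the GAD-7 difference at post-treatment, assessed in both arms before the waitlist arm starts VCBT.
- Correct the within-group time point given as pre-treatment; post-treatment appears to be meant.
- Report 3-month follow-up as within-group maintenance, or as an explicitly labelled comparison of immediate standard with delayed brief VCBT, with no claim against waitlist.
- As a minor change, define completers for the post-treatment between-group effect size by the post-treatment questionnaire alone.

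The cost is wording in the protocol and the registry entry. No visits, measures or participants are added. What is given up is a controlled claim at three months, which the design cannot support.
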